#### Cardiac biomarkers

3.3.3.

Plasma submission for cardiac biomarker analysis is required prior to each chemotherapy cycle, on day 8 of induction 1 and intensification 2 (in LR2 strata receiving mitoxantrone), and at the end of protocol therapy. Subjects treated on Arms C/D with gilteritinib will also undergo biomarker sample collection prior to the start of maintenance, mid-maintenance (week 25), and end of maintenance (Figure 2). Peripheral blood is to be collected in one EDTA tube and one lithium heparin tube. Biomarker assays will be performed *post hoc*; thus, results are not available to sites in real time. High-sensitivity troponin T will be analyzed at a CAP/CLIA-approved biomarker core laboratory the Cleveland Clinic's Center for Cardiovascular Diagnostics and Prevention for analysis using the Elecsys Troponin T Gen 5 STAT and NT-proBNP assays from the Cobas platform (Roche Diagnostics, Indianapolis IN). Assays are highly reproducible, standardized, and FDA-approved for clinical use with coefficients of variation of <10%. Furthermore, blood will also be banked for future assays.

#### Cardiac data reporting

3.3.4.

Cardiac adverse events (e.g., ejection fraction decrease, LVSD, heart failure, QTc prolongation) must be reported by institutions at any grade of severity via the clinical trial data portal RAVE EDC. The site measured the LVEF and LVSF of each echocardiogram, and the uncorrected QT and ventricular rate from each ECG must be reported. Adverse events are classified by site principal investigators according to the National Cancer Institute Common Terminology Criteria for Adverse Events (version 5.0).

### Anthracycline dose modification strategy

3.4.

AAML1831 utilizes an anthracycline dose modification strategy that aims to optimize anthracycline delivery while minimizing cardiotoxicity (Figure 3). Thus, the LVEF threshold for anthracycline dose modification is restricted to clinically significant declines in cardiac function to an LVEF below 50%. In the event of LVSD, the protocol recommends repeating the echocardiogram in 1 week to confirm cardiac dysfunction prior to proceeding with dose modification of anthracycline, if clinically appropriate. Subsequent reinitiation of anthracycline is permitted regardless of whether the episode occurred in the presence or absence of infection as long as the LVEF recovers to ≥50%. In those who require withholding of LVSD, AAML1831 maintains the intensity of protocol therapy by replacing the anthracycline-containing block with a similarly intensive high-dose cytarabine (Capizzi II) block. AAML1831 strongly recommends cardiology consultation and consideration of neurohormonal therapy, such as ACE inhibition or beta-blockade, in those with LVSD, which may help support the recovery of cardiac function (Figure 3). The receipt of cardiac remodeling medications will be collected in study case report forms and allow analysis of their impact on cardiac functional recovery.

**Figure 3 F3:**
[figure not shown]
Approach to anthracycline/anthracenedione (AC) dose modification for left ventricular systolic dysfunction (LVSD) on AAML1831. ^1^EF should be measured by the biplane Simpson's method. If unevaluable, use alternate EF measurement. If EF is unevaluable, use the shortening fraction (SF) threshold of SF < 24%. ^2^Only relevant to AC-containing cycles. For low EF prior to non-AC cycles, may proceed with therapy. Recommend cardiology consultation for consideration of cardiac remodeling medications to support cardiac function. ^3^For patients with persistent LVSD, cardiology consultation is strongly recommended for consideration of cardiac remodeling medications to support the recovery of cardiac function.

### Statistical analysis

3.5.

#### Comparison of cardiotoxicity across arms

3.5.1.

To compare the incidence of LVSD across the entire cohort of non-FLT3 mutant AML subjects treated on Arm A (standard anthracycline plus dexrazoxane) or Arm B (CPX-351), LVSD cases will be identified based on site quantitated LVEF measured on any on-therapy or end of therapy echocardiogram. LVSD will be defined as a biplane Simpson's LVEF < 50%. If the biplane Simpson LVEF is unavailable, LVSD will be defined by a single-plane LVEF measurement, or, if also unavailable, an LVFS below 24%. A time-to-event analysis will be used to compare the cumulative incidence of LVSD between arms. LVEF and GLS declines throughout therapy will be compared across Arm A and Arm B using generalized estimating equations (GEE) including centrally quantitated LVEF and GLS performed at all precycle timepoints, end of therapy, and 12 months off therapy. Similarly, GEE incorporating baseline and post-anthracycline biomarker measurements will also be performed to compare changes in hs-cTnT and NT-proBNP throughout therapy.

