#### Echocardiograms

3.3.1.

Cardiac function will be serially assessed by echocardiograms at baseline, following each subsequent therapy cycle, 12 months following completion of protocol therapy, and at least every 2 years thereafter through 10 years following completion of protocol therapy (Figure 2). Additional echocardiograms are required for patients with FLT3-mutant AML receiving gilteritinib maintenance, including pre-, mid- (week 25), and postmaintenance. Pre-/postcycle echocardiograms are to be performed when the patient has recovered from the toxicities of the previous chemotherapy cycle and ideally when off IV fluids and with evidence of blood count recovery. Echocardiograms are to be performed according to the AAML1831 echocardiogram acquisition protocol, reflective of a contemporary and comprehensive standard-of-care pediatric echocardiogram. Emphasized views include the 2D LV images in the apical four-chamber, two-chamber, and three-chamber views and the parasternal short-axis views at the LV apex, mid-, and basal levels. Site sonographers are recommended to review the AAML1831 echocardiogram acquisition training slides or webinar and undergo a certification process involving detailed feedback from the core lab regarding echocardiogram quality. Echocardiograms are analyzed for LV function at each site per standard-of-care to inform clinical care and safety of ongoing anthracycline delivery. Each site-measured LVEF and LVSF are required to be submitted in the AAML1831 case report forms. DICOM echocardiogram images are submitted to the Penn Center for Quantitative Echocardiography for post hoc quantitation in a blinded fashion. The primary measurements include LVEF derived by biplane Simpson's method, global longitudinal and circumferential strain, and LV wall thickness (LVWT) to LV end-diastolic dimension (LVEDD) ratio. Additional comprehensive measures of cardiac structure and function relating to chamber size, Doppler indices, and valvular disease are also obtained, which will enable important exploratory analyses of the impact of AML therapies on cardiac remodeling, systolic and diastolic function, as well as more novel indices such as regional strain (53, 54). All measures are quantitated using the Tomtec cardiac performance analysis (Unterschleissheim, Germany).

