### Sample size considerations

3.6.

AAML1831 will enroll approximately 1,400 subjects over an estimated 5-year accrual period. The integrated cardiac studies are designed to address cardiac-specific aims within a representative subcohort of the study population with the primary emphasis on comparing the cardiotoxicity across arms. The case cohort is constructed to identify predictors of cardiotoxicity will incorporate cases from the entire study population (analyzing those treated on Arms C/D with gilteritinib separately). Estimating an LVSD rate of 8% in the conventional chemotherapy arm (inclusive of dexrazoxane) based on AAML1031 data and 5% in the CPX-351 arm, 33 cases are anticipated within the subcohort plus an additional 33 cases from the non-FLT3 mutant population (i.e., Arm A/B) outside of the subcohort (*n* = 510). Thus, the overall case cohort will consist of 543 patients, including 66 cases (40 for the standard arm, 26 for the CPX-351 arm). An estimated 33% of the 510 patients included in this analysis will be at high risk; thus, expect 84 high-risk and 171 low-risk patients per arm. Assuming an LVEF standard deviation of 10%, there will be 80% power to determine a difference between treatment arms of 6% LVEF for high-risk patients and 4% LVEF for low-risk patients, accounting for correlations between repeated measures by GEE. Assuming a GLS standard deviation of 2.5%, there will be 80% power to determine a difference between treatment arms of 1.2% GLS for high-risk patients and 1% GLS for low-risk patients.

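### As worded, the Aim 2 GEE appears to compare change from baseline between arms without adjusting for the baseline value, which gives up precision that costs nothing to keep

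*Protocol article*

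**What the plan says.** Section 3.5.1 (Comparison of cardiotoxicity across arms) fixes the model and its data for cardiac aim 2. For echocardiography: "LVEF and GLS declines throughout therapy will be compared across Arm A and Arm B using generalized estimating equations (GEE", with the data described as "including centrally quantitated LVEF and GLS performed at all precycle timepoints, end of therapy, and 12 months off therapy". For biomarkers: "GEE incorporating baseline and post-anthracycline biomarker measurements will also be performed to compare changes in hs-cTnT and NT-proBNP throughout therapy". No covariate, arm-by-visit term, baseline constraint or tested contrast is named.

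Baseline is available for every measure. Section 3.3.1 (Echocardiograms): "Cardiac function will be serially assessed by echocardiograms at baseline, following each subsequent therapy cycle, 12 months following completion of protocol therapy". Section 3.3.3 (Cardiac biomarkers): "Plasma submission for cardiac biomarker analysis is required prior to each chemotherapy cycle", which includes the sample before induction 1.

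Section 3.6 (Sample size considerations) gives the power: "Assuming an LVEF standard deviation of 10%, there will be 80% power to determine a difference between treatment arms of 6% LVEF" in high-risk patients and 4% in low-risk patients, with an allowance for correlated repeated measures. For GLS it assumes an SD of 2.5% and differences of 1.2% and 1%. The groups are 84 high-risk and 171 low-risk patients per arm.

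**The concern.** The echocardiogram before induction 1 is a precycle visit, so on the natural reading it is among the values modelled. The biomarker sentence names baseline outright. If baseline is an ordinary outcome row and each arm has its own baseline mean, a comparison of declines is the difference in mean change from baseline. Randomisation makes the true arm difference at baseline zero. A model that does not use this fact adds the sampling noise of the baseline difference to the estimate.

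Aim 2 is the randomised comparison that rests on blinded core-lab echo measurements, and the Discussion presents central reading as the route to greater precision. Discarding precision in the model works against that purpose, most of all in the high-risk group with only 84 patients per arm.

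**Working it through.** **Inputs.** SDs, differences and group sizes are from section 3.6; 1:1 allocation is from section 3.2. The article gives no significance level, baseline-to-follow-up correlation (rho) or visit count. I assume two-sided 5%, rho of 0.3, 0.5 and 0.7, equal SD at all visits, and equal correlation between visits.

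**1. The stated 80% power.** Plain two-sample formula: SE = SD x sqrt(2/n); power = Phi(difference/SE - 1.96).

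| Comparison | SE | Difference/SE | Power | Difference at 80% power (2.80 x SE) |
|---|---|---|---|---|
| LVEF 6%, n = 84 | 1.543 | 3.89 | 97.3% | 4.32 |
| LVEF 4%, n = 171 | 1.081 | 3.70 | 95.9% | 3.03 |
| GLS 1.2%, n = 84 | 0.386 | 3.11 | 87.5% | 1.08 |
| GLS 1%, n = 171 | 0.270 | 3.70 | 95.9% | 0.76 |

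The 80% is not reproduced. It would need variance inflated by (3.89/2.80)^2 = 1.93, and likewise 1.74, 1.23 and 1.74. Other significance levels and a change-score SD did not reproduce all four figures either. With the significance level, correlation and visit count unknown, this does not show that the statement is wrong.

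**2. One follow-up visit.** In units of SD^2, per-patient variance is 2(1 - rho) for a change score and 1 - rho^2 with baseline adjustment. The ratio is 2/(1 + rho).

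| rho | Change | Adjusted | Ratio | Power of change score if adjusted analysis has 80% |
|---|---|---|---|---|
| 0.3 | 1.40 | 0.91 | 1.54 | 62% |
| 0.5 | 1.00 | 0.75 | 1.33 | 68% |
| 0.7 | 0.60 | 0.51 | 1.18 | 73% |

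Differences detectable with 80% power, change score to adjusted, are 2.80 x SE x sqrt(variance):

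- LVEF, high risk: 5.11 to 4.12, 4.32 to 3.74, 3.35 to 3.09 (rho 0.3, 0.5, 0.7)
- LVEF, low risk: 3.58 to 2.89, 3.03 to 2.62, 2.35 to 2.16
- GLS, high risk: 1.28 to 1.03, 1.08 to 0.94, 0.84 to 0.77
- GLS, low risk: 0.90 to 0.72, 0.76 to 0.66, 0.59 to 0.54

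**3. Mean of five post-baseline visits (count assumed).** With M = (1 + 4 rho)/5, the variance is M + 1 - 2 rho for change and M - rho^2 adjusted:

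- rho 0.3: 0.84 against 0.35, ratio 2.40
- rho 0.5: 0.60 against 0.35, ratio 1.71
- rho 0.7: 0.36 against 0.27, ratio 1.33

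**4. Gain at the article's own differences.** At rho 0.5 and one visit, cutting the variance by 25% moves the step 1 powers from 97.3% to 99.4%, 95.9% to 99.0%, 87.5% to 94.9% and 95.9% to 99.0%. Three of the four gain only 2 to 3 points; high-risk GLS gains about 7.

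**The case against.** The strongest reply is that the article does not specify the model criticised here. The echo sentence never uses the word baseline, and taking baseline into the biomarker model could mean using it as a covariate. A GEE with baseline among the outcomes and a common baseline mean is not excluded, and it is about as precise as covariate adjustment. Exact model terms usually sit in the full protocol or analysis plan, which are not shown. This stands to the extent that the unadjusted comparison is the natural reading, not a stated fact. It does not remove the point: the article does fix the method and the data, and a more precise analysis of the same data is available.

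The gain is also assumption-dependent. Excluding patients with LVEF below 50% narrows the baseline range and may lower rho. A lower rho shrinks the gain over a simple follow-up comparison, but it widens the gain over a change score.

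A reader might infer three stronger things, none of which the documents support:

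- **Dilution toward zero.** A single arm effect averaged over baseline and 4, 5 or 6 later visits would shrink a constant effect to 0.80, 0.83 or 0.86 of its size. The article specifies no such contrast. Section 3.5.1 speaks of declines and changes, and section 2 of changes in serial measures, which points to arm-by-time. Section 3.6 speaks only of a difference between arms, which leaves the contrast unnamed but does not establish averaging over baseline.
- **Bias.** Under randomisation, leaving baseline out costs precision only.
- **A wrong power statement.** It claims an allowance for repeated-measures correlation and does not say whether the SDs are of levels or of changes, so it can be neither confirmed nor refuted.

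**Conclusion.** The point holds as one of efficiency. On its natural reading, section 3.5.1 compares change without using the baseline value as well as it could. If the comparison is an unconstrained arm-by-time contrast, its variance for one follow-up visit is about 1.5, 1.3 or 1.2 times that of a baseline-adjusted contrast at rho 0.3, 0.5 or 0.7. The ratio exceeds 1 at every positive rho below 1, so the direction does not depend on the value chosen, although the size does. The five-visit ratios (2.40, 1.71, 1.33) also rest on an assumed visit count and equal correlation. The weight is low to moderate, because the aim is secondary and no bias or power error is shown.

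**What to change.** In section 3.5.1, state one of two forms:

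- Post-baseline visits only as outcomes, with arm, visit and arm-by-visit terms and the baseline value of the same measure as a covariate (core-lab value for LVEF and GLS, log scale for hs-cTnT and NT-proBNP).
- Baseline kept as an outcome with the arm means constrained equal at baseline. This also retains patients with no readable baseline echocardiogram. It needs a working correlation other than independence, since under independence the constraint brings no precision.

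Name the tested contrast: for LVEF and GLS, the arm difference over post-baseline visits and at 12 months off therapy; for the biomarkers, the difference over the post-baseline samples collected, through end of therapy. Use the same contrast in section 3.6.

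The cost is a sentence or two of wording and no new data. The one practical drawback is that the covariate form needs a rule for missing baselines, which the constrained form avoids.

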#### Cardiotoxicity risk prediction

3.5.2.

For analysis of cardiotoxicity predictors, a case cohort will be constructed composed of a subcohort of sequentially enrolled patients treated on arms A and B (*n* = 510 including 84 high-risk and 171 low-risk patients per arm), plus any additional LVSD cases identified from the Arm A/B study population outside of the subcohort based on site measured LVEF and confirmed on core lab quantitation. LVSD cases will be defined as a centrally measured core lab LVEF < 50% or, if LVEF is not available, LVFS < 24% at any precycle, end-of-therapy, or off-therapy echocardiogram between intensification and 12 months posttherapy.

Among the case cohort (*n* = 543), a series of weighted ordinary least-squares linear regression models will be used to define the association between postinduction 1 GLS and the postinduction 1 change from baseline in GLS (two separate models) and LVEF at 12 months posttherapy (dependent variable). A similar series of regression models will be used to assess the association between on-therapy hs-cTnT and NT-proBNP elevations (predictors) with EF 12 months after therapy (outcome variable).

Subsequently, time-to-event survival models will be used to estimate the relationships of relevant host factors (age, sex, BMI, race) and treatment exposures (cumulative anthracycline dose, anthracycline arm, HSCT vs. chemotherapy alone) with LVSD, defined as core lab quantitated LVEF < 50% occurring on or within 1 year after protocol therapy. After the estimation of the relationship of these host and treatment variables with LVSD, a multi-marker risk prediction model will be developed incorporating significant host factors, treatment exposures, and echocardiographic predictors for the development of LVSD within 1 year of completing therapy. Finally, a separate cohort of children treated on AAML1031 will be retrospectively analyzed to provide external validation for this risk prediction model.

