### Rationale for LVSD case definition

1.3.

Definitions of cardiotoxicity vary according to clinical trials and guidelines. The most commonly accepted definition of clinically significant cardiotoxicity in adults is a >10% decrease in LVEF to an LVEF < 50% (50). Baseline cardiac dysfunction or cardiovascular comorbidities are uncommon in pediatrics, thus pediatric definitions commonly rely on an absolute LVEF or LVFS without taking into account the decline from baseline. The Common Terminology Criteria for Adverse Events (CTCAE) definitions of LVSD have varied over time but have generally defined grade 2 or higher LV dysfunction using an LVEF threshold of 50% (termed “ejection fraction decreased” in CTCAE v. 5). Therefore, LVSD cases will be defined by an LVEF < 50% for all AAML1831 cardiac analyses. The first cardiac aim (described below) includes all subjects treated on Arms A/B using site-measured/reported LVEF to determine LVSD (*n* = ∼1,068). The second cardiac aim is limited to a subcohort of representative subjects who will undergo detailed cardiac phenotyping via core lab echocardiography quantitation and serial cardiac biomarker assessment (*n* = ∼510).

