In addition to primary cardioprotection with dexrazoxane and the use of a liposomal encapsulated anthracycline, AAML1831 employs a rigorous, standardized approach to identifying and managing cardiotoxicity that seeks to balance the potentially competing goals of cardiotoxicity reduction and maximizing anthracycline delivery to optimize both leukemia and cardiovascular outcomes (62, 63). Although challenging, the implementation of a standardized echocardiogram acquisition protocol, comprehensive site echocardiography lab training and regular feedback to optimize the quality of images captured, and the prioritization of LVEF quantitated by the biplane Simpson's method will improve the reliability of cardiotoxicity assessment on which sites are basing the safety of ongoing anthracycline administration. In addition, to maximize the delivery of effective cancer therapy, AAML1831 employs a relatively low threshold for anthracycline dose modification (LVEF < 50%), protocol guidance for a repeat echocardiogram in 1 week to assess for recovery prior to withholding anthracyclines, potential reintroduction of anthracycline therapy in patients with transient LVSD, and recommended cardiology consultation with evidence of cardiotoxicity. Although the optimal method to effectively treat leukemia while preserving cardiac function has not been established, careful attention to this balance is warranted, and this study will provide key data to inform evolving cardioprotective strategies.

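### The case-cohort subcohort is taken by order of enrolment, so about half of the expected LVSD cases may have no sampled non-cases from their own enrolment period

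*Protocol article*

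**What the plan says.** Section 3.5.2 (Cardiotoxicity risk prediction) states the sampling rule: "a case cohort will be constructed composed of a subcohort of sequentially enrolled patients treated on arms A and B". Its size is given as "510 including 84 high-risk and 171 low-risk patients per arm". The rest of the Arm A/B population contributes cases only: "plus any additional LVSD cases identified from the Arm A/B study population outside of the subcohort". Section 1.3 describes cardiac aim 2 as "limited to a subcohort of representative subjects who will undergo detailed cardiac phenotyping", and Section 3.6 also calls the subcohort representative. Nowhere does the article describe random selection, sampling by enrolment period or adjustment for calendar time.

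Section 3.6 gives the planning figures: "Estimating an LVSD rate of 8% in the conventional chemotherapy arm" and "5% in the CPX-351 arm". From these it expects 33 cases inside the subcohort and 33 outside, hence 66 cases in 543 patients, with accrual over about 5 years. Section 1.3 puts the Arm A/B total at about 1,068.

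**The concern.** Case-cohort weights let the subcohort's non-cases stand for all non-cases in the full cohort. Random or stratified random sampling guarantees this by design. A consecutive block does not: a non-case enrolled outside the block has no chance of selection, so no weight can bring that period's non-cases back. The extra cases from the period are nevertheless included.

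Any change in a predictor over accrual then appears as a difference between cases and non-cases. Some change is plausible, because the Discussion describes "comprehensive site echocardiography lab training and regular feedback to optimize the quality of images captured", and GLS, the leading echocardiographic predictor, is measured on those images. Supportive care or case mix could also move over 5 years. At stake are the estimated associations of GLS, hs-cTnT and NT-proBNP with LVSD, and the risk model built from them.

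**Working it through.** **Inputs.** Subcohort 510, or 255 per arm (Section 3.5.2). LVSD rates 8% and 5%, GLS SD 2.5, LVEF SD 10, accrual 5 years (Section 3.6). Arm A/B total about 1,068 (Section 1.3). All drift sizes below are assumptions, because the article gives none.

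**Step 1: reproduce the plan's counts.**
- Inside the subcohort: 255 × 0.08 + 255 × 0.05 = 33.15 (stated 33).
- Outside, with an Arm A/B total of M: (M − 510)/2 × 0.13.
- M = 1,020: 33.15 outside, 66.3 cases, 543 patients. All stated figures reproduce, and 50% of cases lie outside.
- M = 1,068: 36.3 outside, 69.4 cases, 546 patients; 52% of cases lie outside. The stated 66 cases therefore fit a total nearer 1,020, but the share outside hardly changes.

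**Step 2: period covered.** The subcohort is 510/1,068 = 48% to 510/1,020 = 50% of Arms A/B. With uniform accrual and one block it spans 2.4 to 2.5 of the 5 years. The other 2.5 years or so supply cases only.

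**Step 3: case versus non-case contrast.** Let a predictor's mean differ by d between the two periods. About half of the cases and none of the sampled non-cases carry the shift, so the bias is 0.5 × d − 0 × d = d/2.
- d = 0.5 GLS points: 0.25, and 0.25/2.5 = 0.1 SD.
- d = 1.0 GLS points: 0.50, and 0.50/2.5 = 0.2 SD.
- Approximate standard error with 66 cases and 510 − 33 = 477 non-cases: 2.5 × √(1/66 + 1/477) = 0.33. The bias is about 0.8 to 1.5 standard errors.

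An illustrative simulation agrees (1,068 patients, 6.5% cases, a predictor with no effect, weighted logistic model with sandwich errors, 1,000 runs per setting). The logistic model stands in for the time-to-event model.

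| Drift between periods (SD) | Odds ratio per SD, sequential | Type I error, sequential | Type I error, random |
|---|---|---|---|
| 0 | 1.00 | 5.6% | 5.3% |
| 0.2 | 1.11 | 14.5% | 6.8% |
| 0.4 | 1.25 | 40% | 3.9% |
| 0.6 | 1.37 | 66% | 5.0% |

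With a random subcohort the odds ratio stays at about 1.00. Drifts of 0.2 and 0.4 SD correspond to 0.5 and 1.0 GLS points.

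**Step 4: weighted linear models for 12-month LVEF.** With cases weighted 1 and non-cases 1,068/510, the total weight is 66 + 477 × 2.09 = about 1,065. The 33 outside cases carry p = 33/1,065 = 3.1% of it. If cases have a 12-month LVEF lower by D (assumed 8 to 12 points), the gap between outside cases and everyone else is about 0.97 × D, because the rest include some cases. For a predictor with no effect, the absolute slope bias is about p(1 − p) × d × 0.97D / 2.5².
- d = 0.5, D = 8: 0.030 × 0.5 × 7.7 / 6.25 = 0.02 LVEF points per GLS point.
- d = 1.0, D = 12: 0.030 × 1.0 × 11.6 / 6.25 = 0.06.
- Rough standard error of the slope: 10/(2.5 × √543) = 0.17. The bias is about 0.1 to 0.3 standard errors.

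**The case against.** The strongest reply has five parts.

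- **Selection is not on outcome.** Consecutive enrolment does not choose patients by LVSD status, so the weights still work if predictors and risk are stable over accrual. This stands. A reader might infer that the weighted analysis is invalid outright. The article does not support that: the analysis rests on an unverified assumption, and with no drift there is no bias.
- **Measurement is controlled.** Echocardiograms follow one acquisition protocol and are quantitated blinded and post hoc at one core laboratory (Section 3.3.1). Biomarkers are assayed post hoc at one laboratory with coefficients of variation under 10% (Section 3.3.3). This limits reader and assay drift, but not drift in site acquisition, supportive care or case mix. The article expects feedback to improve reliability; it does not say that mean GLS will move.
- **The main GLS models are little affected.** A reader might apply d/2 to every predictor analysis. Step 4 shows that it does not describe the models with continuous 12-month LVEF. For change from baseline in GLS, an additive acquisition shift largely cancels between a patient's two echocardiograms.
- **Some predictors cannot drift through measurement.** Age, sex and race depend only on case mix, and arm is randomised 1:1 throughout.
- **The block is inferred.** The article does not give its start or say that it is unbroken. Intermittent selection would narrow the gap.

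These points narrow the concern but do not remove it. The stated rule still does not deliver the representativeness claimed for the subcohort. External validation on AAML1031 could reveal a poor model but would not correct biased coefficients.

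**Conclusion.** The point holds in a limited form. By the plan's own figures, 33 of 66 expected cases (52% with 1,068 patients) come from outside the subcohort. On the one-block reading, none of the non-cases enrolled alongside them could be sampled. Validity then needs no drift in predictors or risk with enrolment date.

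The exposure is mainly in the LVSD time-to-event and multi-marker risk models: about d/2, or 0.1 to 0.2 SD for an assumed GLS drift of 0.5 to 1.0 points. It is small for 12-month LVEF and smaller still for change-from-baseline GLS.

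A reader might also infer that the randomised comparison of the arms is compromised. It is not: within the subcohort both arms come from the same period, and aim 1 "includes all subjects treated on Arms A/B using site-measured/reported LVEF to determine LVSD". The change is worth making because it is cheap, not because bias has been shown.

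**What to change.** Draw the subcohort at random within arm and enrolment period across all accrual, and say so in Section 3.5.2. Images and plasma are collected from trial patients generally and analysed post hoc, and Section 4 reports accrual still open. The subcohort stays at 510 and the expected case counts do not change.

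If a consecutive block has already been read, keep it as one stratum, sample the unread remainder of the 510 at random from later enrolment, and compute the weights by arm and enrolment period.

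If all 510 have been read, pre-specify a repeat of the predictor and risk models within the subcohort alone, where cases and non-cases share an enrolment period, and state the no-drift assumption of the main analysis.

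Cost: some core-laboratory work moves later in accrual. No extra reads are needed only while part of the 510 is unread. The within-subcohort check has about 33 events instead of 66; the approximate standard error of the GLS contrast rises from 0.33 to 2.5 × √(1/33 + 1/477) = 0.45.
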